**Health**													
	Patient Health Questionnaire-15 [49]	15		✓		✓		✓		✓		✓	
	Graded Chronic Pain Scale-Revised [50]	6				✓		✓		✓		✓	
**Self-regulatory processes**													
	Difficulties in Emotional Regulation Scale-16 [51]	16		✓		✓		✓		✓		✓	
	Multidimensional Experiential Avoidance Questionnaire-30 [52]	30		✓		✓		✓		✓		✓	
	Attention Control Scale [53]	20		✓		✓		✓		✓		✓	
	Flexible Regulatory Emotional Expression Scale [54]	16		✓		✓		✓		✓		✓	
	Identity Coherence Scale [55]	12		✓		✓		✓		✓		✓	
	Response to Stressful Experiences Scale [56]	22		✓		✓		✓		✓		✓	
**Supportive relationships**													
	PROMIS-Emotional Support 4 Scale [57,58]	4		✓		✓		✓		✓		✓	
	PROMIS-Informational Support 4 Scale [57,58]	4		✓		✓		✓		✓		✓	
	PROMIS-Instrumental Support 4 Scale [57,58]	4		✓		✓		✓		✓		✓	
	DRRI-2^i^ Unit Support Scale [59]	12		✓		✓		✓		✓		✓	
**Personality**													
	Multidimensional Personality Questionnaire-Brief Form [60]	155		✓									
	Triarchic Psychopathy Measure [61]	58		✓									
**Vulnerability or risk factors**													
	Adverse Childhood Experiences Questionnaire [62]^j^	17		✓						✓			
	DRRI-2 Prior Stressors Scale [59]	18		✓									
	DRRI-2 Adapted Postdeployment Life Stressor Scale [59]	14				✓		✓		✓		✓	
	Suicidal Ideas and Behaviors Questionnaire [63]	6		✓									
	Basic Training Stressors Scale [23]	14				✓							

^a^Baseline, before basic combat training.

^b^2 weeks after basic combat training.

^c^6 months after basic combat training.

^d^12 months after basic combat training.

^e^18 months after basic combat training.

^f^PROMIS: Patient Reported Outcomes Measurement Information System.

^g^PTSD: posttraumatic stress disorder.

^h^DSM-5: Diagnostic and Statistical Manual of Mental Disorders, Fifth Edition.

^i^DRRI-2: Deployment Risk and Resilience Inventory-2.

^j^Adverse Childhood Experiences Questionnaire adapted for youths at time 0.

#### Outcomes

Primary outcomes include trajectories of internalizing symptoms, externalizing problems, social-occupational functioning, and global adaptive functioning. Secondary outcomes are self-reported self-regulatory processes, neurobehavioral markers of self-regulation, and ecologically valid markers of functioning extracted from administrative military records.

#### Neurocognitive Measures

Table 2 lists the neurobehavioral functions and major cognitive domains assessed by tests from the PCNB administered at baseline. Neurocognitive tests measure performance accuracy (eg, proportion of correct responses) and speed (eg, median correct response time) in major cognitive domains [64].

**Table 2 table2:** Neurobehavioral functions and domains assessed using tests from the Penn Computerized Neurocognitive Battery at baseline in the Advancing Research on Mechanisms of Resilience longitudinal study.

Neurobehavioral Function	Domain	Test
Executive control	Attention	Penn Continuous Performance Test
Complex cognition	Language reasoning	Penn Verbal Reasoning Test
Episodic memory	Face memory	Penn Facial Memory Test
Social cognition	Emotion differentiation	Penn Emotion Differentiation Test

### Laboratory Substudy Procedures

A subsample of the longitudinal cohort (123/1201, 10.24%) was recruited for a laboratory visit, both before and after BCT. Laboratory participants were selected based on their responses to baseline self-report measures and a predictive algorithm developed in the pilot UG3 phase of this project (details reported elsewhere; [name] et al, unpublished data, 2023). This strategy was intended to provide a subsample enriched with participants at a relatively high risk of maladaptive functioning (~72/123, 58.5%) compared with a low-risk group (~48/123, 39%). Participants were briefly screened via phone call, and those reporting contraindications to MRI due to the potential presence of metal in the body (eg, participants employed as a metal worker or participants with implanted medical devices) or due to problems with being in enclosed places were excluded.

Data for the laboratory substudy were collected during an 8- to 9-hour combined pre-BCT laboratory visit to the MVAHCS and UMN Center for Magnetic Resonance Research and during a 4- to 5-hour post-BCT laboratory visit at the MVAHCS. During the pre-BCT and post-BCT laboratory visits, participants completed a structured clinical interview (1-2 hours) with a trained master’s level assessor under the supervision of a licensed clinical psychologist ([name] or [name]). The Structured Clinical Interview for Diagnostic and Statistical Manual of Mental Disorders, Fifth Edition (DSM-5) was used to diagnose lifetime mental disorders and determine whether the disorder is “current” [65]. The Clinician-Administered PTSD Scale for DSM-5 was used to diagnose PTSD [66]. Participants also completed a battery of self-report measures assessing constructs related to self-regulation (Table 3).

**Table 3 table3:** Self-report measures administered in the Advancing Research on Mechanisms of Resilience laboratory substudy before and after basic combat training (BCT).

Measure	Items, n	Pre-BCT laboratory visit	Post-BCT laboratory visit
Patient Health Questionnaire-9 [67]	9	✓	✓
Beck Depression Inventory-II [68]	21	✓	✓
Depressive Symptom Index-Suicidality Subscale [69]	4	✓	✓
State Trait Anxiety Inventory [70]	40	✓	✓
Positive and Negative Affect Schedule [71]	20	✓	✓
Multidimensional Experiential Avoidance Questionnaire [72]	62	✓	✓
Anxiety Sensitivity Index [73]	16	✓	✓
Intolerance of Uncertainty Scale-Short Form [74]	12	✓	✓

Participants were asked to complete an EEG session to measure resting-state neural function as well as brain responses during cognitive tasks. We used electrodes embedded in an elastic cap to record electrical activity from 128 scalp sites. The precise physical location of the electrodes was recorded in 3D space with respect to auricular and nasion landmarks so that EEG recordings could be integrated with the corresponding structural MRI data. To measure eye movements for the detection of bioelectrical artifacts, vertical electro-oculograms were recorded from above and below the right eye, and horizontal electro-oculograms were recorded from near the outer ocular canthi. Left and right forearm electromyographs and electrocardiograms were recorded to identify and reduce artifacts and quantify the aspects of muscle contraction associated with button presses. EEG signals were digitized at the rate of 512 Hz with 0.5-200 Hz low frequency and 200 Hz high frequency bandpass filters. Each participant completed assessments of visual acuity and handedness as well as provided information about medications, alcohol consumption, caffeine consumption, and sleep in the last 24 hours. Self-report ratings of emotional state were assessed before and after EEG recording sessions using the Positive and Negative Affect Scale [71].

At the pre-BCT laboratory visit only, MRI data were collected at the UMN’s Center for Magnetic Resonance Research on a 3T (Siemens) Prisma scanner using a 32-channel birdcage head coil with foam pads to minimize head movements. Sequences included T1-weighted Magnetization Prepared-Rapid Gradient Echo, T2-weighted Sampling Perfection with Application optimized Contrast using different flip angle Evolution, diffusion-weighted MRI, resting-state functional MRI (fMRI), and task-based fMRI.

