### Statistical Methods

Aim 1 will characterize adaptation among young military recruits over the first 2 years of service. Consistent with a hierarchical concept of the structure of resilience, we will use latent growth mixture modeling to identify the latent trajectories of adaptation and its indicators. We will apply latent growth mixture modeling at the level of internalizing symptoms, externalizing problems, and social-occupational functioning as well as an overall model that simultaneously embeds all 3 domains into a model of adaptive functioning. We hypothesize that at least three trajectories (one showing resilient adaptive functioning or low pathology and the other two showing new-onset and chronic distress) will emerge for each domain assessed (internalizing symptoms, externalizing problems, social-occupational functioning, and global adaptive functioning).

Note that all remaining analyses for aims 2 and 3 will be conducted on the trajectory class membership data for each of these 4 domain outcomes to test for the specificity of resilience mechanisms***.***

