Aim 2 will identify the promotive factors and protective processes contributing to individual variations in adaptation. We will apply structural equation modeling and Bayesian network analysis to detect and identify the latent constructs and the dependency structure between different domains. We will also examine the effects of protective and vulnerability factors on membership in different trajectory classes. We propose to investigate this in 2 complementary ways. First, in our structural equation modeling, we will augment the measurement submodels of the most parsimonious latent growth structural mixture models accepted in aim 1 with the indicators of protective and vulnerability measurements (Tables 1 and 2) and evaluate the change in the relationships (coefficients) that indicators have with the latent trajectories. We will treat potential predictors as moderators or mediators, depending on their hypothesized role in the model, and we will test their contribution to the model by change in model fit indices using the Akaike information criteria (AIC), the Bayesian information criteria (BIC), root mean squared error (RMSE), and goodness-of-fit (G^2^) also known as the likelihood ratio test. Second, the trajectory class membership assignment in aim 1 will be used as dependent variables (resilient vs nonresilient or distressed trajectories), and protective and vulnerability factors will be used as predictors in random intercept multinomial logistic mixed models that will provide a quantitative picture of the unique contribution of these measures. We hypothesize that the risk factors listed in Tables 1 and 2 will predict membership in nonresilient or distressed trajectory classes, whereas protective or promotive factors will predict membership in the resilient or nondistressed trajectory classes. All analyses will be estimated within the propensity classes that adjust for any possible lack of imbalance and will be performed on both complete cases and 5 imputed data sets.

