Aim 3 will investigate whether neurobehavioral markers of self-regulation assessed using a series of performance-based tasks involving EEG and fMRI assessments are predictive of resilient and nonresilient trajectories. EEG recordings will be put through an independent component analysis–based processing pipeline to isolate and remove noisy time segments, signal artifacts (eg, eye movements), and bad electrodes. Recording epochs centered around the onset of task stimuli will be extracted for the analysis of event-related potentials and time-frequency energy. Given that this study focuses on conflict monitoring and bottom-up covert attention, we plan to examine brain responses at midline frontal (eg, FCz) and lateralized posterior electrodes (eg, PO7 and PO8), respectively. We will quantify brain response metrics such as feedback-related negativity and θ-band (4-8 Hz) oscillations, which we predict will be associated with trajectory class membership. fMRI data collected during the farmer task will be analyzed using an event-related design to model blood oxygenation level dependent (BOLD) fluctuations due to stimuli onsets using Analysis of Functional Neural Images software [82]. Functional activation maps will be computed by regressing each voxel’s fMRI response time course onto an ideal response function for 5 stimulus types: the danger cue, 3 classes of safety cues with parametrically varying levels of perceptual similarity to the danger cue, and a control condition including a safety cue with no perceptual similarity to the danger cue [83]. We will focus particularly on fMRI responses to these stimuli in brain areas associated with fear reactivity (anterior insula and dorsomedial prefrontal cortex) and fear inhibition (ventromedial prefrontal cortex and anterior hippocampus). Fear-related brain activations to safety cues resembling danger cues (relative to safety cues without danger-cue resemblance) will be used as predictors of maladaptive avoidance (costly or unnecessary avoidance of safe cues perceptually resembling danger cues). Finally, these brain and behavioral responses, as well as their moderation by protective (eg, social support, military cohesion, and self-regulation) and vulnerability factors (eg, BCT stressors and anxiety traits), will be used as predictors of trajectory class membership.

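### Aim 3 does not condition on the baseline risk score used to select the laboratory subsample, so a marker that only tracks questionnaire risk can appear to predict trajectory class

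*Protocol article*

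**What the plan says.** **Selection.** Under Laboratory Substudy Procedures: "A subsample of the longitudinal cohort (123/1201, 10.24%) was recruited for a laboratory visit". The same section explains that "Laboratory participants were selected based on their responses to baseline self-report measures and a predictive algorithm developed in the pilot UG3 phase". The purpose was to enrich for people at higher risk of poor adaptation. The split is about 72 high risk and 48 low risk. How the low-risk group was drawn is not stated.

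**Outcome.** Under Statistical Methods: "Note that all remaining analyses for aims 2 and 3 will be conducted on the trajectory class membership data", for each of four domains. The Self-Report Variables section and Table 1 show that the symptom and functioning questionnaires are given from time 0 to time 4 and serve to track the outcome trajectories.

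**Aim 3 model.** The EEG, fMRI and task measures "will be used as predictors of trajectory class membership". Moderators are to be tested too, named by example only: support, cohesion and self-regulation on the protective side, training stressors and trait anxiety on the vulnerability side. No risk group, algorithm score or test of value beyond the baseline questionnaires is named.

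**Nearest adjustment.** The Aim 2 paragraph ends with: "All analyses will be estimated within the propensity classes that adjust for any possible lack of imbalance". The classes are not defined and laboratory selection is not mentioned.

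**The concern.** The selection score was built to predict maladaptive functioning, which is what the trajectory classes describe. Selection and outcome also share a source, baseline self-report. A recruit with raised symptoms at time 0 is more likely to be labelled high risk and more likely to fall in a chronic-distress class. Any EEG or fMRI measure that correlates with baseline symptoms will then be associated with class, whether or not it carries information of its own.

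This bears on what Aim 3 can claim. The Abstract speaks of pathways through which self-regulation markers contribute to adaptation, and the Conclusions look ahead to interventions. The model as stated cannot separate a marker's contribution from the questionnaire risk already known at recruitment.

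**Working it through.** **1. The article's own figures.** 123/1201 = 10.24%; 72/123 = 58.5%; 48/123 = 39.0%. All reproduce. 72 + 48 = 120, so the split is 60:40 among those classified (both counts are approximate).

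**2. Hand check of the mechanism and of the role of enrichment.** Assumptions, not in the article: nonresilient class in 40% of high-risk and 10% of low-risk participants; marker mean 0.3 SD higher in the high-risk group; no marker effect within a risk group. H denotes high risk.

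Marker difference between classes = [P(H | nonresilient) − P(H | resilient)] × 0.3; odds ratio per SD ≈ exp(difference).

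- 60% high risk: nonresilient share 0.6×0.4 + 0.4×0.1 = 0.28. P(H | nonresilient) = 0.24/0.28 = 0.857. P(H | resilient) = 0.36/0.72 = 0.500. Difference 0.357×0.3 = 0.107; OR ≈ 1.11.
- Random sample with 20% high risk: nonresilient share 0.2×0.4 + 0.8×0.1 = 0.16. P(H | nonresilient) = 0.08/0.16 = 0.500. P(H | resilient) = 0.12/0.84 = 0.143. Difference 0.357×0.3 = 0.107; OR ≈ 1.11.

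The spurious association is the same in both samples. It comes from leaving out risk, not from the 60:40 mix. Simulation at n=123 agrees: with 40% vs 10% and 0.3 SD, or 50% vs 10% and 0.5 SD, the unadjusted OR is 1.11 to 1.23 with 8-18% rejection at 0.05, against 4-5% after adjustment for risk group.

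**3. Simulation with a continuous risk score.** 120 participants are drawn from 1201 as 72 high and 48 low risk, and the marker has no effect on class once the score is known. Assumptions: OR 3 per SD of score on distressed class; marker-score correlation 0 to 0.5; about 22-24% distressed in the cohort; high-risk share of the cohort 15-40%.

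Unadjusted rejection at 0.05, with a 25% high-risk share of the cohort:

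| Sample | Correlation 0.3 | Correlation 0.5 |
|---|---|---|
| Simple random | 24% | 55% (OR 1.62) |
| 72/48, low risk drawn from everyone else | 24-27% | 61-63% (OR 1.58-1.59) |
| 72/48, low risk drawn from the opposite tail | 53-54% | 92-93% (OR 1.93-1.96) |

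At correlation 0 the rate is 4-5%.

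Across high-risk shares of 15-40% and correlations of 0.3-0.5:

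| Analysis | Rejection |
|---|---|
| Unadjusted, low risk from everyone else | 24-72% |
| Unadjusted, low risk from the opposite tail | 30-99% |
| Adjusted for the two-level risk group | 5-13% |
| Adjusted for the continuous score | 4-6% |
| Sampling weights only (low risk from everyone else) | 26-60% |

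The 72% occurs at a 15% high-risk share and correlation 0.5. The OR there is 1.65, close to the 1.62 of a random sample, so enrichment barely changes the association itself.

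**4. Would the stated moderators suffice?** Adjusting for a vulnerability covariate that correlates 0.6 with the score (assumed) still leaves 13-50% rejection at the 25% share.

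**The case against.** **This is a condensed article.** Covariate lists are normally left to a fuller plan, the Aim 3 text does not say the models are unadjusted, its moderators include vulnerability factors, and the propensity-class sentence refers to all analyses. That stands in part: the full plan may already adjust. But Aim 3 is specified down to electrodes, frequency band, brain regions and predictor types, with the selection score absent. The moderators are examples and not the score itself. The propensity sentence belongs to the Aim 2 paragraph and leaves its classes undefined.

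**Aim 3 asks only whether markers predict, not whether they add to questionnaires.** This is fair as a reading of the Objectives, and it is why the unadjusted association should be kept. It does not support the Abstract's language of pathways and contribution.

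**Adjustment may remove real signal.** If the score shares items with the time-0 outcome measures, conditioning on it removes part of the outcome. This stands and shapes the fix.

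**Stronger readings that the article does not support.**
- A reader might infer that markers will look predictive. That requires correlation with the score, which is not documented.
- A reader might blame the enriched mix. Step 2 gives the same odds ratio in a random sample, and opposite-tail sampling is only a possibility.
- A reader might treat weights as an alternative to adjustment. They leave 26-60% rejection.
- A reader might object that class frequencies in the laboratory sample misstate the cohort. The classes come from the Aim 1 models of the longitudinal cohort, and no prevalence estimate from the 123 is announced.

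**Conclusion.** The concern holds in a limited form. Selection on a baseline risk score is documented, the outcome also rests on time-0 self-report, and the stated Aim 3 model does not condition on that score. A marker that merely tracks questionnaire risk can then be reported as a predictor of trajectory class.

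The simulated figures show direction and range, not expected results. They rest on an assumed odds ratio, marker-risk correlation, class prevalence and cohort risk share, none of which the article gives. The firm conclusions are qualitative: no inflation without a marker-risk correlation, a material rise with a moderate one, near-complete removal by the continuous score, partial removal by the two-level group, and no removal by weights alone. Aim 3 is a secondary objective, so this limits how its findings can be interpreted and leaves Aims 1 and 2 untouched.

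**What to change.** - In every Aim 3 model of class membership, add the algorithm's continuous score as a covariate. If it is unavailable, use the risk stratum and acknowledge some residual confounding.
- Report each marker's contribution beyond the score beside its unadjusted association, and say which supports which claim.
- State how low-risk participants were drawn, whether the score shares items with the time-0 outcome measures, and whether the propensity classes apply to Aim 3.
- Use inverse-sampling weights only if an estimate from the laboratory sample is meant to describe the whole cohort. The weights would have to reflect the adult age limit, the phone and MRI screening and the pandemic suspension as well as the score. They could not be formed if the middle of the score range was never sampled.

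**Cost.** One covariate, which should be on file because it was used for selection. Marker effects may shrink, partly through overlap between the score and time-0 outcome items; this is why both estimates should be shown.

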### Neurobehavioral Assessments

#### Overview

During the EEG session at the pre- and post-BCT visits, participants were asked to perform a series of neurobehavioral tasks applying paradigms to assess attentional control (dot-probe paradigm) [75,76], emotional inhibitory control (go or no-go paradigm) [77,78], and feedback processing (gambling decision paradigm) [79]. In addition, participants were asked to complete a video game–based task applying the Pavlovian-instrumental generalization paradigm [80] to assess adaptive versus maladaptive avoidance in the face of a physical threat.

#### Dot-Probe Task

Attentional bias is assessed using the dot-probe task [75,76]. Participants passively inspect rapidly presented face pairs with neutral, happy, or angry and threatening expressions. The face pairs disappear and are replaced by a blank space on one side of the screen and an asterisk (target probe) on the other. Participants are instructed to respond as quickly as possible to indicate the side on which the target probe appeared.

#### Emotional Go or No-Go Task

Inhibitory control is assessed using the emotional go or no-go task [77,78]. Participants view a series of rapidly presented visual targets and nontargets. Participants are instructed to press a response button for each target presented (“go trials”) and to avoid pressing the button for each nontarget (“no-go trials”). Errors (response to no-go trials or failure to respond to go trials) are accompanied by visual (red bar in the center of the screen) feedback. The task is completed in 3 blocks with adaptive response timing windows to increase task difficulty based on performance. Participants are provided with visual feedback on task points earned or lost, which is displayed on the screen every 20 trials. During the second block, time windows are shortened to increase the task’s difficulty just beyond what is feasible for participants. Points awarded during the second block for correct responses are also significantly reduced.

#### Gambling Decision Task

Error and performance monitoring is measured using the gambling decision task [79]. For each trial, participants are presented with 2 adjacent squares, each enclosing a number (5 or 25). Participants are instructed to choose between the 2 squares and then receive feedback (the chosen box turns red or green to signify either a win or a loss, with the winning and losing colors counterbalanced across participants). Winning and losing squares are preprogrammed in a randomized manner such that participants must make guesses and will be unable to detect a true pattern using the task feedback. Thus, the task assesses participant biases toward risk-taking following the experience of loss.

